### Phase 2: Development of a Chronic Disease Management model for initiation of insulin in the community and intensification of blood glucose control

The medication algorithm is broken into stages and can be found in Additional File 1: Initiation of metformin, initiation of sulphonylurea, initiation of thiozolidendiones and finally initiation of insulin followed by multidose insulin. A plan of management for diabetes intensification will be prepared for each patient based on their stage at their enrollment into phase 3, the treatment phase of the study. This plan will describe the dietary and lifestyle intervention they will receive as well as the planned stage for medication for the diabetes intensification. Prior to initiating each stage of medical therapy, a letter will be sent to the Primary Care physician including the results of the blood glucose monitoring. The letter will indicate the stage of diabetes intensification recommended and will include a standardized Home Care order set for that stage. The order sets were reviewed with some of the local primary care physicians during invited continuing education sessions about the DreamTel program. Once the Primary Care physician has reviewed this and signed the order set this stage of diabetes intensification will begin. When the stage of intensification of diabetes has been completed the Home Care team will notify the Primary Care physician. If the patient has achieved diabetes targets they will be maintained at this stage. If they have not achieved target then the orders for the next stage will be sent to the Primary Care physician and the patient assessed for the next stage.

Algorithms developed for diabetes management were developed based on clinical practice guidelines and reviewed with experts in diabetes management. For self monitoring of blood glucose[1], the goal is a minimum of four times daily, two days per week for those on or starting insulin. Medication will be introduced in a stepped fashion for those on diet therapy alone starting with metformin followed by a sulphonylurea (gliclazide, as it is better tolerated in patients that develop kidney disease than others)[53], thiazolidendiones (TZD's) will be added if sulphonylureas have failed. Pioglitazone (Actos) was chosen for use as it is a once daily preparation. This step was added prior to the controversy over rosiglitazone[54]. The algorithm for diabetes intensification to be carried out by the Home Care team was incorporated into a standardized order form for the primary care physician to approve. The study team in partnership with the primary care physician will be responsible for assessing contraindications to the algorithms.

The initiation of insulin is often frightening for patients and a program of education and an algorithm for the introduction of insulin were developed. At all times, the primary care physician will be kept in the loop as part of a management model. After Home Care visits, reports on study letterhead will be faxed or mailed to the primary care physician. In addition, a system of graded alerts developed by the Home Care team including the use of the existing Provincial emergency Health Hotline and medical backup will be used in the study.

The goal of this phase of the program is to facilitate a change of practice to improve diabetes management over the long term. Physicians and the Home Care team need to become integrated and systems developed to do this. The hope is that following the study, patients who require diabetes intensification will be identified by the physician, the Home Care team and possibly by patients themselves. The Primary Care Physician would then initiate the process by signing a completed Home Care referral form for the initiation of intensification of diabetes management. This will initiate a visit by the Home Care team (nurse or dietitian).

Following three months with the device, if patients are testing at 80% of the target for measurement, they will be enrolled in the next phase of the program and receive diabetes intensification therapy. At this point, following the first phase, patients willing to participate in the program will received a physical exam and assessment of their current diabetes status and medications with a specialist and a determination on which part of the diabetes intensification algorithm they are in.

In the Province of Saskatchewan there is a billing code for the supervision of diabetes intensification. Educational sessions for the primary care physicians will include the rationale for the DreamTel study, a review of the protocol itself and information on this billing code and its appropriate use for the management of these patients. It is a goal of the DreamTel study that the Primary Care physicians will be able to continue to work with the Home Care team for the intensification of diabetes management after the project has been completed.

Home care referral forms were developed for the primary care physicians. It was planned that if the primary care physician did not want the Home Care team to do the intensification of diabetes management according to the planned algorithm that the subjects would be followed as a control. If the primary care physician directs the Home Care team to manage the patients in a similar fashion, only using different medications from the algorithm, based on patient specific factors, these patients will remain in the study. Referrals to the local diabetes education centre will be tracked if any occur. The commencement date for intensification will be recorded. Intensification is defined as increasing the dosage of a medication, adding another medication or initializing insulin according the algorithm for intensification.

For clients on oral anti-hyperglycemic agents, designated RN(s) who are part of the Home Care team will adjust these medications based on the protocol. Off-standard situations will be reviewed with one of the specialist study physicians.

### Phase 3: Achieve better control of blood glucose levels

Rationale. Based on the success of the DREAM study where a chronic disease management model resulted in improved blood pressure control[7], the DreamTel study hopes to demonstrate that a chonic disease management program can improve glycemic control in First Nations People with diabetes.

Experimental Design: The main intervention will be applied to the treatment group and will consist of diabetes management intensification including a stepped drug protocol algorithm for pharmacologic management of blood glucose including the addition of insulin when indicated, diet and lifestyle education, with the long term goal of achieving A1c levels of ≤ 7.0%. (see Additional File 1)

The study is designed as a pilot consisting of fifty subjects. Subjects entering this phase of the study will have type 2 diabetes and will have used the LifeStat blood glucose monitoring device for 3 months. Subjects will have completed at least 80% of all recommended glucose meters readings and will have been agreeable to intensification of diabetes according to the treatment algorithm. Diabetes intensification includes as needed, the initiation of oral hypoglycemic agents, the addition or increase of dosage of oral hypoglycemic agents and the initiation and dose titration of insulin. A1c levels will be drawn on a three-monthly basis. If fewer subjects than anticipated make it through phase 1 and are eligible for phase 3, additional subjects will not be recruited. As this is a pilot study, the reasons that fewer subjects than expected are able or willing to enroll into phase three will be explored.

All patient information specific to diabetes management from each Home Care visit to implement the intensification protocols will be forwarded to the patient's family physician. Follow-up with the patient's primary care physician will be requested by the Home Care team with each medication change to ensure that they are aware of the patient's new treatment status, and that it corresponds to their desired treatment goals for that patient. The Home Care team will be responsible for attempting to maintain ongoing contact with their clients if their clients accept that contact. Participants will be provided with snacks and meals as well as health-promotion materials part of current protocols. Additionally the study sponsor provided gifts such as t-shirts and mugs for study visits to see the study investigators, part of preexisting health promotional activities.

The initial assessment will include lab testing and historical information to address risk factors for cardiovascular-renal disease. The results of all testing will be forwarded to the primary care physician; subsequently, protocol-driven therapy for blood sugar control will begin. Medication doses and compliance will be closely monitored and prescriptions will be adjusted, as necessary. In the DREAM3 study, 45% of subjects had A1c levels ≥ 8.0%[7].

This investigation will be conducted in North Battleford, Saskatchewan. The DreamTel nurse coordinator will be based at the Battlefords Tribal Council Health Care services in North Battleford and will coordinate all aspects of the study under the supervision of [name]. [name] will be responsible for the diabetes management algorithm. Data collection and management will be coordinated by [name]. A data clinical research assistant, based in Toronto, will be responsible for the monitoring, data collection and data entry. Statistical analysis will be performed at the Institute for Clinical Evaluation (ICES) in Toronto.

### Inclusion criteria

Type 2 Diabetes with baseline A1c ≥ 7.0% on diet or medical therapy with no history of diabetic ketoacidosis. Patients must be greater than or equal to 18 years of age. Written informed consent must be obtained prior to admission to this study.

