### Phase 1: Introduce the Bluetooth-enabled glucose meters into the community

Experimental Design. The target populations for the DreamTel study are participants with Type 2 diabetes and uncontrolled blood glucose levels with A1c levels in excess of 7.0%. Fifty subjects are targeted in the pilot study. Clients willing to participate in the program who have uncontrolled diabetes based on A1c levels above target will receive information on the use of the Bluetooth enabled device and will be consented into the project. They will then have the device installed into their home and receive training on its use from the Home Care team. Technical support is available from the sponsor. For the first phase, lab testing for A1c takes place at initiation of the device and after three months. Subjects will be identified by their primary care physician or by the Home Care team as needing diabetes intensification. Thus they will constitute a convenience sample. Subjects will be trained in the use of the glucose meters but do not have to be taking insulin on enrollment. All will be trained on the Bluetooth technology. The LifeStat service is an Integrated Communications Technology to capture physiological data that is transmitted via Bluetooth to an aggregation device located at the point of care. The aggregation device can be a cell phone but in the DreamTel study due to insufficient local coverage a Bluetooth/Analog modem with the local telephone will be used. The data is then forwarded to a secure hosting center by standard telephone network. The information is then accessed by users with the appropriate credentials through a care giver portal.

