All subjects receiving the device will have a multi-disciplinary team diabetes assessment with standard diabetes screening tests including a baseline A1c level and agree to follow-up lab work on a three-month basis throughout the duration of the study. Each study subject will receive training in how to use the device and will be instructed on how to indicate that a test run was a validation test or another person's sample. Subjects will be instructed to use the results of the testing to manage their diabetes according to the education they received in light of food intake (or lack of), physical activity and whether medication had been taken. The client will be taught how to use the device and how to demonstrate that they were able to accurately use it. Data forwarded to the web server will be displayed through the portal graphically and include summary statistics. Data can also be printed by the patient's health care providers and could became part of the client's medical record. All consenting subjects will be asked to notify their primary care physicians that they are using the new device during regularly scheduled visits. Their physicians will also receive information packages from the Home Care team on the study and will be invited to participate in local Continuing Health Education programs on the study and the technology used. To determine whether the installation of the LifeStat device linked to the patient's telephone line impacts on blood glucose control, the A1c level at baseline (prior to its installation) will be compared to the three-month value. Typically A1c levels remain stable over short periods of time, rising over a period of years[45].

To provide data on whether the blood glucose monitoring was before or after a meal, a teleprompt will be delivered to the client's phone. When a blood glucose result is received by the central server at SaskTel's central office in Saskatoon, Saskatchewan, an automatic teleprompt will call requesting a response as to the relationship between the test result and the last food intake. The teleprompt was developed in English and in Cree. Patients will be trained in its use. Each patient's impression of the teleprompt system will be addressed in questionnaires administered after the first 3 months of its use. Learning challenges will be collected as qualitative data to record the duration of time spent teaching and to record the challenges faced.

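### Phase 1 credits the 3-month A1c change to the device, but nothing secures stable drug treatment around baseline, so the result supports only device plus concurrent usual care

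*Protocol article*

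**What the plan says.** The protocol article, under Phase 1, gives the purpose of the comparison: "To determine whether the installation of the LifeStat device linked to the patient's telephone line impacts on blood glucose control". The method is that "the A1c level at baseline (prior to its installation) will be compared to the three-month value". There is no concurrent control. The justification follows at once: "Typically A1c levels remain stable over short periods of time, rising over a period of years".

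The same section describes how subjects arrive: "Subjects will be identified by their primary care physician or by the Home Care team as needing diabetes intensification". It adds: "Thus they will constitute a convenience sample". The Inclusion criteria section then admits "Type 2 Diabetes with baseline A1c ≥ 7.0% on diet or medical therapy with no history of diabetic ketoacidosis", with adult age and written consent as the other conditions. No minimum time on an unchanged regimen is required.

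Physician care continues during Phase 1: "All consenting subjects will be asked to notify their primary care physicians that they are using the new device during regularly scheduled visits". Physicians also receive information packages and invitations to education sessions, and providers can print the transmitted readings.

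Medication tracking appears in two places. The Phase 2 section records when intensification starts and defines intensification by reference to the algorithm, which is applied after Phase 1. The Phase 3 section says that doses will be closely monitored, in its text on protocol-driven therapy.

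**The concern.** In an uncontrolled before-after comparison, the assumption about what would have happened anyway does the work of a control group. Here the assumption is a flat A1c over 3 months. That is reasonable for people on settled treatment. It is doubtful for people selected because someone has just judged that their treatment should be stepped up, since that judgement can itself lead to a prescription.

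Two routes follow. A drug started or titrated shortly before baseline may still be lowering A1c when the baseline sample is taken, so part of its effect lands in the 3-month change. A drug changed by the usual physician during the 3 months acts inside the window directly. As the plan is described, both are counted for the device.

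At stake is the Phase 1 claim, repeated in the abstract, that this phase will show whether using the device changes A1c. The 6-month primary outcome is not the main casualty.

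**Working it through.** **Does the stability premise fit the selected population?** Setting the statements side by side:

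- Premise: A1c is flat over short periods (Phase 1 section).
- Selection: a treatment change is judged due (Phase 1 section).
- Eligibility: any diet or medical therapy, with no stable period (Inclusion criteria).
- During follow-up: regular physician visits continue, and no text holds treatment constant or separates out changes (Phase 1 section).
- Recording: tied to algorithm-driven intensification after Phase 1 (Phase 2 and Phase 3 sections).

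Nothing in the text makes the premise hold for these subjects.

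**How large could the shift be?** The article gives a target of 50 subjects. It gives no alpha, power, effect size or SD and refers to an additional file that is not shown, so there is no planned figure to reproduce. Everything below except n = 50 is an assumption.

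Let f be the share of subjects with a drug change and e the A1c fall from that change expressed between the two tests. With no device effect, the mean fall is f × e.

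- Low end: 0.20 × 0.5 = 0.1 points.
- High end: 0.40 × 1.0 = 0.4 points.
- If only half of each effect falls between the tests: 0.05 to 0.2 points.

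The only related figure in the article is in its Discussion: among specialist-referred patients, more than 50% were not intensified within four months of a high A1c, so fewer than 50% were. That is another population and does not fix f here.

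**How does this compare with what 50 subjects can detect?** Assume a paired comparison, two-sided alpha 0.05, normal approximation, and an SD of the 3-month change of 1.0 to 1.5 points.

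- Detectable difference at 80% power = (1.960 + 0.842) × SD / √50. This is 0.40 points for SD 1.0 and 0.59 for SD 1.5.
- Chance of a significant result with an inert device: s = √(SD² + f(1 − f)e²), t = f × e / (s/√50), probability = Φ(t − 1.960) + Φ(−t − 1.960).

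| f | e | Mean fall | Probability, SD 1.5 | Probability, SD 1.0 |
|---|---|---|---|---|
| 0.20 | 0.5 | 0.10 | 7.5% | 10.7% |
| 0.20 | 1.0 | 0.20 | 15% | 26% |
| 0.30 | 1.0 | 0.30 | 27% | 49% |
| 0.40 | 0.5 | 0.20 | 15% | 28% |
| 0.40 | 1.0 | 0.40 | 43% | 72% |

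Worked example (f = 0.40, e = 1.0, SD 1.0): s = √(1 + 0.24) = 1.114; t = 0.40 / (1.114/7.071) = 2.54; probability = Φ(0.58) = 0.72.

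At the low end the false-positive rate is barely above the nominal 5%. At the high end the shift reaches the lower end of the detectable range.

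**The case against.** **Drug changes after baseline are partly the device's own effect.** The abstract, the Background and the Phase 1 section all present the device as a way of getting readings to providers. A prescription prompted by a transmitted reading belongs to the pathway under study. Restricting the main comparison to subjects with unchanged treatment would remove that pathway and select on something influenced by glucose response. This stands, and it rules out the restricted set as the main analysis. It does not rescue the present wording, because changes before baseline, and later changes unrelated to the readings, are not device effects.

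**This is a condensed article.** Medication fields and analysis sets commonly sit in other documents, and their absence here is not the point. The point is the attribution and its stated premise, both of which are in the text and fit the text's own selection rule poorly.

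**The size is assumed, and local practice suggests few changes.** The Background describes clinical inertia and no specialist backup, and subjects are identified as still needing intensification. A change well before baseline would already be partly in the baseline value, and one late in Phase 1 would be only partly expressed by month 3. All this stands: the upper figures need many changes with full expression in the interval.

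**A reader might infer that Phase 3 is compromised too**, because some entrants would already be intensified. The documents do not support that as a main finding. Phase 3 does not claim a common untreated start: each plan is based on the patient's stage at Phase 3 entry, and after Phase 1 a specialist assesses current diabetes status and medications. In Phase 3, drug change is the intervention.

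**The article acknowledges the limits** of a pilot and a convenience sample. It does so in general terms and does not name this confounding.

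**Conclusion.** The point holds for the Phase 1 device question. The plan reads an uncontrolled 3-month A1c change as the effect of installing the device, on a premise that its selection and eligibility rules do not secure. Drug changes shortly before baseline or during the 3 months can contribute to that change.

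The documents do not give the size. The illustrative shift of 0.1 to 0.4 points rests on 20% to 40% of subjects having a change whose full 0.5 to 1.0 point effect falls between the two tests; partial expression makes it smaller. The comparison with detectable effects rests further on the assumed SD, alpha and power.

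Two stronger readings go too far. The documents do not show that the Phase 1 result will be biased by any particular amount, and they do not support treating every drug change in the window as unrelated to the device. Any effect on Phase 3 is secondary. This is a low-cost improvement to what Phase 1 can conclude, in a pilot whose primary outcome lies elsewhere.

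**What to change.** 1. Record each glucose-lowering drug start, stop and dose change, with dates, from 3 months before the baseline A1c to month 3.
2. Keep the comparison in all subjects as the main Phase 1 result, and state its conclusion as the effect of the device together with concurrent usual care.
3. Add two supporting analyses: subjects with no drug change in the 3 months before baseline, and subjects with no change from then to month 3. State that the second selects on post-baseline treatment that the transmitted readings may have prompted.

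None of this changes eligibility or restricts physicians' care. The cost is one case report form item and less precise subsets. If 20% to 40% of 50 subjects had a change in the full window, the unchanged group would number 40 to 30. At the same SD, its standard error would be larger by a factor of √(50/40) = 1.12 to √(50/30) = 1.29.

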### Analytic procedures and sample size calculation

This is a pilot study that will compare, in a before and after methodology, the intervention of diabetes intensification on the primary response variable of blood glucose level (A1c) measured at baseline and at 6 months. The pilot study will also determine the ability to enroll patients into the study and determine how many are able to maintain an 80% adherence rate to the use of the glucose meter four times daily at least twice weekly. This is also a goal of phase 3 of this study. See Additional file 2 for statistical design considerations.

Initiation of Diabetic Medication Treatment: The goal of Intensification therapy is A1c <7.0%. Patients in the usual care arm will continue to see their primary care physicians. Therapy in the treatment group will be initiated with the goal to bring the fasting plasma glucose ≤ 6 mmol/L and in insulin treated patients, pre-meal glucose concentrations of 4–7 mmol/L.

Safety and Interim Monitoring. Drug therapy may be interrupted at any time during the trial if further evidence for more appropriate drug therapy becomes available. All drugs used in this trial are available in regular clinical practice. Women of child-bearing potential must have a negative urine pregnancy test prior to receiving study medication. Patients will be asked for adverse events from the last visit related to hypoglycemic episodes and these data recorded. In the UKPDS 33 study the rates of major hypoglycemic episodes per year were 0.7% with conventional treatment, 1.0% with chlorpropamide, 1.4% with glibenclamide, and 1.8% with insulin [48,49]. Severe hypoglycemia defined as needing the assistance of another person, or coma, will be tracked, as will diary-recorded instances.

Case report forms, confidentiality, data security and monitoring. Case report forms will be completed by the study nurse in Saskatchewan and faxed to the coordinating centre in Toronto after all patient identifiers have been removed; data monitoring will be completed on each visit. The original forms will be kept on file at the Battlefords Tribal Council Indian Health Services. All data is owned in collaboration with the Battlefords Tribal Council Indian Health Services. All work for publication from this data will be shared with this group prior to submission and requests for aggregate data will be honored as quickly as resources permit. At all times the Investigators have the final responsibility for the accuracy and authenticity of all clinical data entered on the CRF's. The study will be conducted according to the Battlefords Tribal Council Indian Health Services Ethical Guidelines for Research and the principles of Ownership, Control, Access, Possession[55]. The Data Coordinator/Monitor will conduct site visits four times annually at a mutually agreed upon time for the purpose of auditing the study. The local investigator and clinical coordinator agree to allow the monitoring of the clinical supplies storage area and study documentation.

Approvals. The Battlefords Tribal Council Indian Health Services Inc has passed a Tribal Council Resolution approving the implementation of the DreamTel study. Ethics approval has been obtained from the Sunnybrook Health Sciences Centre and the BTC Research Ethics Boards. (see Additional file 3)

Study subjects will be followed from study entry until study completion (18 month study protocol from the start of phase 1). The primary outcome of this phase of the study is the A1c after 6 months. A1c results collected beyond this will be analyzed if there are sufficient subjects. Subjects may withdraw from the study at any time. Subjects who refuse or are unable to adopt the recommendations of diabetes intensification management will be followed in an intent-to-treat fashion.

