**Methods and design:**

The study population will consist of patients with type 2 diabetes with uncontrolled A1c levels living on reserve in the Battlefords region of Saskatchewan, Canada. This pilot study will take place over three phases. In the first phase over three months the impact of the introduction of the Bluetooth enabled glucose monitor will be assessed. In the second phase over three months, the development of guidelines based treatment algorithms for diabetes intensification will be completed. In the third phase lasting 18 months, study subjects will have diabetes intensification according to the algorithms developed.

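### The primary A1c change has no stated starting point and the article's timings conflict; if the only dated baseline is used, the change mixes the device effect and regression to the mean with intensification

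*Protocol article*

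**What the plan says.** Under *Analytic procedures and sample size calculation* the study compares, "in a before and after methodology, the intervention of diabetes intensification", using "the primary response variable of blood glucose level (A1c) measured at baseline and at 6 months". Later in the same part of the article, after the approvals, it adds: "The primary outcome of this phase of the study is the A1c after 6 months". The sentences just before that one count follow-up as 18 months from the start of phase 1.

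Elsewhere, baseline A1c is used in two ways:

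- *Phase 1*: "the A1c level at baseline (prior to its installation) will be compared to the three-month value". This is the test of whether the device alone changes A1c. The same section says "lab testing for A1c takes place at initiation of the device and after three months".
- *Inclusion criteria*: "Type 2 Diabetes with baseline A1c ≥ 7.0% on diet or medical therapy".

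The start of intensification is also given in two ways:

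- *Abstract, Methods and design*: phase 1 lasts three months, then "In the second phase over three months, the development of guidelines based treatment algorithms for diabetes intensification will be completed", then phase 3 lasts 18 months.
- *Phase 2*: after three months with the device, patients who meet the testing target qualify, and "they will be enrolled in the next phase of the program and receive diabetes intensification therapy".

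The *Phase 2* section also says that the date on which intensification begins is recorded. The *Phase 1* and *Phase 3* sections schedule A1c every three months. Neither the recorded date nor any of these samples is named as the origin of the primary comparison.

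**The concern.** The primary result is meant to describe what intensification does to A1c. A reader who follows the article's own use of the word baseline arrives at the enrolment value, taken before the device and required to be at least 7.0%. A change measured from there has three components: what the device and its training did (the separate phase 1 question), the fall expected in people chosen because a measurement was high, and intensification. The month 0 to month 3 change would then count twice, once as the phase 1 result and again inside the primary result.

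The primary comparison is before-after. The article mentions patients followed as controls and under usual care, but this comparison does not use them, so nothing subtracts the first two components. The article's remark that A1c is stable over short periods answers a worry about drift. It does not answer regression to the mean after selection on a threshold.

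The end point is as open as the start. How much intensification lies behind a month-6 value depends on which clock is used.

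**Working it through.** The target of 50 subjects comes with no effect size, SD, alpha or power in the article (it refers to Additional file 2, which is not shown), so it cannot be reproduced. The point does not depend on it.

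**Step 1: the timelines.** The Abstract gives 3 + 3 + 18 = 24 months. The later statement gives 18 months from the start of phase 1. With 18 months in total, phase 3 would last 18 − 6 = 12 months on the Abstract's phase sequence, or 18 − 3 = 15 months on the *Phase 2* timing. Neither equals the 18 months that the Abstract gives it.

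**Step 2: intensification contained in month 6.** Exposure = month of reading − month in which intensification starts, in months since device installation.

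| Clock for the 6 months | Intensification starts | Reading | Exposure |
|---|---|---|---|
| Device installation | month 6 (Abstract, phases in sequence) | month 6 | 0 months |
| Device installation | month 3 (*Phase 2*) | month 6 | 3 months |
| Start of intensification | month 3 | month 9 | 6 months |
| Start of intensification | month 6 | month 12 | 6 months |

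**Step 3: regression to the mean if the enrolment value is the baseline.**

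Inputs:
- Entry threshold 7.0% (*Inclusion criteria*).
- 45% of subjects with A1c of 8.0% or more in an earlier study by the group (*Phase 3*), used only to place the centre of the distribution.
- Assumptions, not in the article: A1c normally distributed, SD 1.5 to 2.0, test-retest correlation ρ 0.7 to 0.9.

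Formulas: μ = 8.0 − 0.126 × SD, so that 45% lie at or above 8.0. With a = (7.0 − μ)/SD, the mean of those selected is μ + SD × φ(a)/(1 − Φ(a)). The expected fall with no true effect is (1 − ρ) × (selected mean − μ).

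- SD 1.5: μ = 7.81, selected mean 8.54, difference 0.73. Expected fall 0.3 × 0.73 = 0.22 (ρ 0.7), 0.2 × 0.73 = 0.15 (ρ 0.8), 0.1 × 0.73 = 0.07 (ρ 0.9).
- SD 2.0: μ = 7.75, selected mean 8.90, difference 1.15. Expected fall 0.35 (ρ 0.7), 0.23 (ρ 0.8), 0.12 (ρ 0.9).

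The range is 0.07 to 0.35 points. For scale, with 50 subjects and an assumed SD of change of 1.0 to 1.5, the 95% confidence interval has a half-width of 1.96 × 1.0/√50 = 0.28 to 1.96 × 1.5/√50 = 0.42. At the upper end the artefact is about as large as the precision of the estimate. At the lower end it is small.

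The device effect would come on top. The article gives no size for it, and phase 1 exists to measure it.

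**The case against.** The strongest reply is that the intended comparison is clear enough. A before-after study of intensification most naturally means before and after intensification. The second statement of the primary outcome is specific to a phase, and the *Phase 3* section places an initial assessment with laboratory tests ahead of protocol-driven therapy. The pre-installation baseline carries its own qualifier because it serves the phase 1 question. Additional file 2 may define the anchors, and an article may leave such detail to it.

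Much of this stands. Six months of phase 3 is the likely intent, and a missing definition alone would not be a finding. What remains is that the stated passages conflict. The initial assessment is not called baseline and does not name A1c, while the two passages that do use the term for A1c point to enrolment. The 24 and 18 months cannot both hold, whatever the additional file says.

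A reader might infer more than the article supports:

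- *That the primary comparison contains no intensification.* This needs both a device-start clock and phase 2 counted as three months of patient time. The *Phase 2* timing gives three months of exposure, and the likely intent gives six.
- *That the primary result is biased, with an inflated false-positive rate.* The bias follows only if the enrolment baseline is used. Its size rests on an assumed SD and correlation and on a percentage from an earlier blood pressure study. The article states no hypothesis test.
- *That a phase 3 entry value would be unselected.* Entry requires 80% of the recommended readings and agreement to intensify, so that value is less selected, not free of selection.

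**Conclusion.** The point holds as a conflict in the text that leaves the primary estimate undetermined. The article does not anchor its primary A1c contrast, and its statements on baseline, start of intensification and total duration do not agree. It does not show that the trial will use the wrong baseline.

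If the enrolment value were used, the bias would favour apparent benefit from selection alone, by roughly 0.07 to 0.35 A1c points under the stated assumptions. The direction follows from selecting on the baseline; the size is illustrative. The phase 1 device effect, of unknown size, would be included as well. Re-anchoring takes out the phase 1 contribution and much of the threshold selection. It does not turn an uncontrolled before-after comparison into one that isolates intensification.

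**What to change.** - Define the primary baseline as the last scheduled A1c before the recorded date on which intensification begins.
- Count six months from that date, with a stated visit window. With A1c drawn every three months, some sample lies within 1.5 months of any target date, provided follow-up continues past it.
- State the date to use for subjects who enter phase 3 but never begin intensification, for example the phase 3 entry date. The article follows subjects who do not adopt intensification by intention to treat, and they would otherwise have no time origin.
- Report the change from the pre-device value to month 3 separately, as the phase 1 result.
- Reconcile the timing statements in the Abstract, the *Phase 2* section and the follow-up paragraph of *Analytic procedures and sample size calculation*. Which schedule applies is for the investigators to state.

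The cost is wording, since the samples are already scheduled and the start date is already recorded. The expected change will be somewhat smaller because it no longer includes what happened before intensification. A piecewise mixed model of all A1c values, with separate slopes before and after the start, is optional. With only two or three values before intensification, the first of them selected on the threshold, its early slope would itself absorb regression to the mean.
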